## Abstract

**Background:**

During leisure activities young people are often exposed to excessive noise levels resulting in an increase of noise-induced symptoms such as hearing loss, tinnitus and hyperacusis. Noise-induced tinnitus is often perceived after loud music exposure and provides an important marker for overexposure as a temporary threshold shift that is often not experienced by the individual itself. As oxidative stress plays an important role in the pathogenesis of noise-induced hearing loss, the use of antioxidants to prevent hearing damage has recently become the subject of research.

**Methods:**

This study proposes a randomized, double-blind, placebo-controlled crossover trial to assess the effects of a prophylactic combination of *N*-acetylcysteine (600 mg) and magnesium (200 mg) prior to leisure noise exposure in young adults. The primary outcome measure is the tinnitus loudness scored by a visual analogue scale (VAS). Secondary outcome measures are the differences in audiological measurements for the antioxidant treatments compared to placebo intake. Audiological testing comprising of pure tone audiometry including frequencies up to 16 kHz, distortion product otoacoustic emissions, transient-evoked otoacoustic emissions and speech-in-noise testing will be performed prior to and within 7 hours after noise exposure. By use of a mixed effects statistical model, the effects of antioxidants compared to placebo intake will be assessed.

**Discussion:**

As adolescents and young adults often do not use hearing protection while being exposed to loud music, the use of preventive antioxidant intake may provide a useful and harmless way to prevent noise-induced hearing damage in this population. Furthermore, when exposed to hazardous noise levels the protection provided by hearing protectors might not be sufficient to prevent hearing damage and antioxidants may provide additive otoprotective effects. Previous research mainly focused on occupational noise exposure. The present study provides a protocol to assess the usefulness of antioxidants during leisure noise activities.

**Trial registration:**

The present protocol is registered at ClinicalTrials.gov: NCT01727492.

## Background

Adolescents and young adults frequently expose themselves to hazardous noise levels during social events or through personal listening devices. This has led to an increase of noise-induced symptoms such as noise-induced hearing loss (NIHL) and noise-induced tinnitus (NIT) over the last few years [1,2]. Although 15% to 18% of the young population already experiences permanent NIT and the majority acknowledge the fact that loud music can damage the hearing, the use of hearing protection remains very low [3-5].

Oxidative stress plays a crucial role in the pathogenesis of NIHL and NIT. During excessive noise exposure, the outer hair cells endure metabolic depletion leading to accumulation of reactive oxygen species (ROS) and reactive nitrogen species (RNS) which may ultimately lead to necrosis and apoptosis [6]. While necrosis is a passive form of cell death, usually occurring after gross physical or chemical insult, associated with cell swelling and eventually causing cell rupture and loss of function, apoptosis is an active way of cell death which also occurs under normal metabolic circumstances [7]. However, when apoptosis is ‘forced’ (for example as a consequence of noise exposure) and by this initiated at the wrong time, crucial healthy outer hair cells may die [7].

Under normal circumstances, the human cochlea contains molecules including vitamins, glutathione, enzymes and reactive transcription, which work together to form a complex and sophisticated defense mechanism against oxidative molecules [8]. In cases of excessive noise exposure, the naturally occurring antioxidant systems may not render sufficient detoxifying effects, leading to the possible important role of antioxidant treatment after acoustic trauma [9,10].

While antioxidant treatment for noise-induced hearing damage has often been the subject of animal research [11-17], well-performed human randomized controlled trials remain scarce. Examining the literature, two antioxidants have been mainly investigated as prophylactic prevention in animal and also some human studies: *N*-acetylcysteine (NAC) [18-21] and magnesium (Mg^2+^) [22,23]. As oxidative stress triggers several cascades, it has been proven that a combination of antioxidants may provide better effects compared to a single antioxidant [24]. Most human antioxidant studies have mainly investigated the effects during occupational noise exposure [25]. Hence, the use of prophylactic antioxidants during recreational noise is unclear. As the use of hearing protection does not always render sufficient protection while exposed to hazardous noise levels, an addition of antioxidants may reduce noise-induced symptoms in young people.

The present article proposes a protocol for a clinical study consisting of a double-blind, randomized, placebo-controlled trial with a combination of NAC and Mg^2+^ as prophylactic antioxidants in adolescents during leisure noise exposure. The present report will follow the guidelines expressed by Consolidated Standards of Reporting Trials (CONSORT).

## Design

This study proposes a randomized, double-blind, placebo-controlled crossover trial. Participants need to spend at least 3 consecutive hours in an environment where loud music is played (>95 dB(A)) after taking either a combination of antioxidants (NAC and Mg^2+^) or a placebo, 1 hour prior to noise exposure. Each participant needs to repeat this procedure four times (interval between trials at least 4 days) and each participant will receive twice the antioxidants as well as the placebo. This study aims to investigate the combined effects of NAC and Mg^2+^ by use of four repeated treatments on the hearing of noise-exposed young adults.

### Recruitment

We are recruiting students by advertisements sent by email and distributing information sheets around the University of Antwerp (Antwerp, Belgium). The aim is to always investigate groups (at least two individuals) of peers going out together and therefore attending the clinic within the time range of 7 hours after noise exposure. It is assumed that the pressure of peers also participating in the study will reduce the risk of drop-out. In addition, at the stage of enrolment it will be determined which occasions the subjects will attend and test moments will be scheduled. The aim is to plan all treatments within the range of 3 months in order to reduce the risk of drop-out.

### Treatment protocol

Participants will receive an antioxidant combination of NAC and Mg^2+^, or a placebo drug (sugar pill). The antioxidant packets contain two pills of each 300 mg NAC and 100 mg Mg^2+^. Both pills, providing a total dose of 600 mg NAC and 200 mg Mg^2+^, should be taken orally 1 hour before noise exposure with a large glass of water. In 50%, the packets contain a placebo with an identical appearance and weight as the antioxidants. All participants (as well as the researchers) will be blinded to the order of antioxidants and placebo. The effects of NAC and Mg^2+^ at the respective doses of 600 mg and 200 mg will be analyzed as well as the effects of the combined product, for which no significant adverse effects have been reported in the past. Adverse events are defined as symptoms occurring after the administration of antioxidants or placebo that were not necessarily related to the intervention. Participants will receive a telephone number to report adverse events during the study and will be urged to come to the clinic in case of serious adverse events.

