### Outcomes

The primary outcome measure will be the score on the VAS for tinnitus loudness, which will be measured pre-noise exposure (at the time of antioxidant intake) and 1 hour after noise exposure. The assumed expectation is a drop of 50% of the tinnitus loudness in the antioxidant group compared to the placebo group.

The secondary outcome measure is the evaluation of a significant difference in test results of the audiological testing (audiometry, otoacoustic emissions and speech-in-noise tests) when comparing the placebo results to the antioxidant trials.

A series of audiological tests (described in the following paragraphs) will be performed prior to and within 7 hours after each noise exposure.

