## Discussion

As adolescents and young adults often do not use hearing protection while being exposed to loud music, the use of preventive antioxidant intake may provide a useful and harmless way to prevent noise-induced hearing damage in this population. Furthermore, when exposed to hazardous noise levels the protection provided by hearing protectors might not be sufficient to prevent hearing damage and antioxidants may provide additive otoprotective effects. Previous research mainly focused on occupational noise exposure. The present study will assess the usefulness of antioxidants during leisure noise activities.

The authors acknowledge the limitation of not including blood samples in the present protocol in order to control for naturally varying Mg^2+^ levels in the individual. However, the investigators considered that it was very likely that the drop-out rate would be very high when participants needed to give a blood sample at every test moment, which would be eight in total. It is also assumed that it is the acute increase of NAC and Mg^2+^ prior to noise exposure that provides the extra otoprotective effects and not so much the naturally high or low levels.

To our knowledge, this study is the first to combine NAC and Mg^2+^ as prophylactic antioxidants for noise-induced tinnitus and noise-induced hearing damage in young people performed in a randomized, placebo-controlled trial. Furthermore, both participants and investigators will be blinded for the sequence of antioxidants and placebo. Thus, this would not influence on one hand the participants in rating the tinnitus loudness and on the other hand the investigators in performing the audiological testing, limiting investigator bias as far as possible.

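### The only adverse-event routes described depend on the participant making contact, although eight scheduled test moments per person would allow the same question to be asked in every session

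*Protocol article*

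**What the plan says.** The Treatment protocol section of the article gives both a definition and a method. The definition is wide: "Adverse events are defined as symptoms occurring after the administration of antioxidants or placebo that were not necessarily related to the intervention". The method has two parts: "Participants will receive a telephone number to report adverse events during the study", and participants "will be urged to come to the clinic in case of serious adverse events". No other route is described.

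The schedule provides regular contact. Under Recruitment, groups of peers are expected to be "attending the clinic within the time range of 7 hours after noise exposure". Under Outcomes, the audiological tests "will be performed prior to and within 7 hours after each noise exposure". The Discussion counts the test moments when it explains why no blood is drawn: participants would have had to "give a blood sample at every test moment, which would be eight in total". Under Design, "each participant will receive twice the antioxidants as well as the placebo".

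The measurements described for these occasions are the tinnitus VAS and the audiological tests. The Outcomes section lists no safety outcome. The Abstract and the Discussion both say that preventive intake "may provide a useful and harmless way to prevent noise-induced hearing damage".

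**The concern.** The definition and the capture method do not fit each other well. The definition takes in every symptom, however mild and whatever its cause. The method relies on a participant deciding that a symptom is worth a telephone call. A young adult who feels slightly unwell after an evening at a loud event, perhaps after the one or two drinks that are allowed, may well not call, most of all if the symptom seems unrelated to the pills.

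What is at stake is tolerability information in healthy young people. Each person takes each treatment twice under double-blinding, so symptoms asked for in the same way every time would give a clean within-person description. Symptoms collected only from callers give counts that cannot be turned into rates, because nobody knows what share was reported. A small number of calls could then be taken to mean that little happened.

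**Working it through.** The article states no adverse-event rate, no safety sample size and no safety power, so there is no figure of its own to reproduce. The check sets the method beside the schedule and then measures what few or no reports could mean.

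**Inputs from the article.** Planned number of participants: 21 (Sample size calculation and statistical analyses). Sessions per person: 4, of which 2 antioxidant and 2 placebo (Design). Test moments: 4 × 2 = 8 (Discussion).

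**Assumed inputs.** The fraction *s* of events that participants report (1, 0.5, 0.3, 0.25) and the true event risks. The article gives neither.

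**Step 1: no events, full capture.** All 21 participants receive the antioxidant, so *n* = 21 for a per-person risk.
- One-sided 95% upper bound: 1 − 0.05^(1/21) = 0.133.
- Upper limit of the two-sided 95% exact interval: 1 − 0.025^(1/21) = 0.161.

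**Step 2: no events reported, partial capture.** If a fraction *s* is reported, the one-sided bound on the true risk is the step 1 bound divided by *s*.
- *s* = 0.5: 0.133 / 0.5 = 0.266.
- *s* = 0.25: 0.133 / 0.25 = 0.532 (using the unrounded 0.1329).

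**Step 3: chance of recording nothing when the true per-person risk is 10% (assumed).** The formula is (1 − 0.10 *s*)^21.
- *s* = 1: 0.90^21 = 0.109.
- *s* = 0.5: 0.95^21 = 0.341.
- *s* = 0.3: 0.97^21 = 0.527.

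**Step 4: effect on a comparison between treatments.** Suppose true risks per session of 20% and 5%, with the same *s* under both treatments, as blinding makes plausible. The illustration uses 2 × 21 = 42 sessions per treatment, treated as independent, and an approximate two-sided 5% test of two proportions.

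| *s* | Recorded risks | Risk ratio | Risk difference | Approximate power |
|---|---|---|---|---|
| 1 | 20% v 5% | 4.0 | 15 points | 0.55 |
| 0.5 | 10% v 2.5% | 4.0 | 7.5 points | 0.29 |
| 0.25 | 5% v 1.25% | 4.0 | 3.75 points | 0.16 |

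The ratio is unchanged. The loss falls on absolute rates, on the difference and on precision. The power column is illustrative only, since sessions within a person are correlated.

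**Step 5: what a change part-way through could still deliver.** Trial status reports that half the needed participants had been included. If 10 or 11 remain, no solicited events among them gives a one-sided 95% bound of 1 − 0.05^(1/10) = 0.259 or 1 − 0.05^(1/11) = 0.238.

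**The case against.** The strongest objection is that this is a condensed article. It does not say that the telephone line is the sole route, and questions asked at visits may be set out in the full protocol. A reader might infer that events are recorded only if someone telephones. The text does not support that: attendance for serious events is also named, and silence about visits does not prove that nothing is asked there. What remains is that the article does describe a capture method, and every part of it is started by the participant.

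Three further objections also narrow the point.
- A reader might speak of a compromised safety comparison. None is planned: the outcomes are tinnitus loudness and the audiological tests. The point concerns a description that the design would permit.
- A reader might infer that passive reporting biases antioxidant against placebo. With participants and researchers blinded, under-reporting need not differ by treatment, and step 4 shows the ratio intact when it does not.
- A reader might take harmlessness as a conclusion that the trial intends to draw from its own adverse-event data. The phrase is hedged, was written before any results, and the safety basis stated in the Treatment protocol section is past experience. Sample size alone would also prevent that conclusion, as step 1 shows, and better questioning would not cure it.

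It is also fair to say that the gain is limited for a trial already half recruited (step 5). None of this removes the case for asking a short question at visits that take place anyway.

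**Conclusion.** The point holds in a limited form. The described capture method is weak for the definition it serves, and the visits needed for a better one are already scheduled. Under-recording of mild symptoms is probable, but its extent is unknown.

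The consequence is less informative absolute rates, risk differences and confidence limits, and not necessarily a biased relative comparison. If half of events went unreported, a record with no events would be compatible with a true per-person risk of up to 26.6%, against 13.3% with full capture. The reporting fractions, the 10% risk and the 20% v 5% contrast are assumptions that show the range; only the 13.3% and 16.1% bounds rest on the planned 21 participants alone.

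This is worth changing because the change is cheap. It does not threaten the primary analysis.

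**What to change.** In the Treatment protocol section, keep the telephone line. Add that blinded staff ask the same open adverse-event question at each post-noise visit and again at the next pre-noise visit, and record the answer against the packet number. If the full protocol already requires this, one sentence saying so is enough. After the fourth session no further pre-noise visit follows, so later symptoms from that session still depend on the telephone.

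Report events descriptively per session by treatment, with exact confidence limits. Show sessions collected before and after the change separately, because the two methods capture different shares of events. Do not present the trial as evidence of harmlessness; give the observed rate and its upper limit.

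The cost is one to two minutes per visit, a page in the case report form and a short amendment. More trivial symptoms will be recorded, and sessions already completed gain little.

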### Permitted and prohibited concomitant treatments

The use of alcohol and tobacco is limited to a maximum of two alcohol consumptions and no to two cigarettes. Other psychoactive drugs are strictly prohibited.

### Inclusion criteria

The inclusion criteria are as follows:

• Age between 18 and 28 years old (males as well as females).

• Experience of temporary tinnitus after leisure noise exposure in the past scoring at least 5 or more on a visual analogue scale (VAS) for loudness.

• Willing to attend an indoor/outdoor music event with mean noise levels ≥95 dB(A) LAeq, 60 min for at least 3 consecutive hours.

### Exclusion criteria

The exclusion criteria are as follows:

• Middle ear pathologies such as otitis media and the perforation of the tympanic membrane and history of such pathologies.

• Known allergies for NAC or Mg^2+^.

• Adolescents using hearing protection.

• Recreational noise exposure within 4 days prior to a study trial.

### Randomization

The production of the antioxidant and placebo packets as well as the randomization of the ABAB protocol will be performed by an independent pharmacist. The packets of antioxidants and placebos will be labeled with a number corresponding with the numbers on the forms. The randomization file will be put into a sealed envelope and retained in a safe at the pharmacy. The randomization table will not be available for assessment by anyone else involved in the study. At the end of the study the envelope will be requested.

### Sample size calculation and statistical analyses

A power calculation was performed in order to make an estimation of the sample size needed to detect significant differences in the VAS between the experimental and control group by use of the software G-Power. A two-sided paired *t*-test for mean differences was performed in which an α-level of 0.05 and a nominal power of 80% were used. Assuming a minimal difference of clinical effect of 0.5 between the pre- and post-noise measurements on the VAS, a non-parametric calculation showed a requirement of 21 participants.

All data in this trial will be assessed with SPSS Statistics version 20.0 (SPSS, Chicago, IL, USA) and SAS version 9.1.3 (SAS, Cary, NC, USA). Because multiple correlated measurements will be performed in the same participants, a mixed effects model will be applied. This analysis is preferable over more traditional approaches such as repeated measures analysis of variance (ANOVA) because of the advantages to deal with missing values. The main analysis will be fully specified before unmasking.

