#### Main outcome measure

##### Visual analogue scale (VAS)

Tinnitus loudness will be scored on a VAS from 0 to 10 (0, no tinnitus at all; 10, extremely loud tinnitus, could not possibly be louder), once at the time of antioxidant (or placebo) intake (1 hour prior to exposure) and once 1 hour after noise exposure. At both occasions the VAS will be undertaken in a quiet room.

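### The 0.5 used to size the trial is worded as a pre- versus post-noise difference, so the 21 participants at 80% power are not tied to the antioxidant-versus-placebo hypothesis

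*Protocol article*

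**What the plan says.** All text is in the Protocol article.

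- *Sample size calculation and statistical analyses* gives the purpose of the calculation: it is "needed to detect significant differences in the VAS between the experimental and control group".
- The method follows: "A two-sided paired *t*-test for mean differences was performed in which an α-level of 0.05 and a nominal power of 80% were used".
- The effect and the result come in the next sentence: "Assuming a minimal difference of clinical effect of 0.5 between the pre- and post-noise measurements on the VAS", and then "a non-parametric calculation showed a requirement of 21 participants". No unit is attached to 0.5, and no standard deviation is given.
- *Outcomes* states the treatment hypothesis: "The assumed expectation is a drop of 50% of the tinnitus loudness in the antioxidant group compared to the placebo group".
- *Visual analogue scale (VAS)* sets the scale: "Tinnitus loudness will be scored on a VAS from 0 to 10". The score is taken at intake, 1 hour before exposure, and again 1 hour after exposure.
- The only loudness level in the article is in *Inclusion criteria*, for past tinnitus: "scoring at least 5 or more on a visual analogue scale (VAS) for loudness".

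**The concern.** Pre-noise and post-noise scores are two readings from the same night under the same treatment. A paired test of one against the other asks whether loud music raises tinnitus loudness. A rise is to be expected on both treatments, because the trial recruits people who have had marked temporary tinnitus after noise. Power for that question is not power for antioxidant against placebo.

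The hypothesis in *Outcomes* is on the right contrast, but it is a relative effect with no placebo mean to convert it to points. A reader cannot tell what treatment difference 21 participants were meant to detect, or with what power. If the trial finds no significant difference, the 80% claim cannot be used to say which effects it was well placed to find.

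**Working it through.** **Step 1. The contrasts side by side.**

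| Place | Contrast as worded | Size |
|---|---|---|
| Sample size section, purpose | experimental vs control | none |
| Sample size section, effect entered | pre-noise vs post-noise | 0.5, no unit |
| Outcomes | antioxidant vs placebo | 50% lower, no placebo mean |

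Rows 1 and 3 agree on the contrast. Row 2, which carries the number, does not.

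**Step 2. Can 21 be reproduced?** Inputs from the article: two-sided α = 0.05, 80% power, paired t-test, effect 0.5. The SD of the paired differences is missing, so 21 cannot be derived from stated inputs. It can only be solved backwards.

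Power = P(|T| > t(0.975, n−1)), where T is noncentral t with n−1 degrees of freedom and noncentrality (Δ/SD)·√n.

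- For n = 21 and 80% power, Δ/SD must be 0.643, so the noncentrality is 0.643 × √21 = 2.95.
- If Δ = 0.5 VAS points, SD = 0.5/0.643 = 0.78 points.
- With a Wilcoxon signed-rank test and normal differences (efficiency 3/π), Δ/SD must be 0.659 and SD = 0.5/0.659 = 0.76 points. This is relevant because the article calls the calculation non-parametric after naming a t-test.

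**Step 3. If 0.5 is a standardised effect.** With Δ/SD = 0.5, the two-sided t-test needs n = 34. At n = 21 the noncentrality is 0.5 × 4.583 = 2.29 and power is 59%. The two-sided Wilcoxon needs 35 (normal), 31 (logistic), 39 (minimum efficiency) or 23 (Laplace). A one-sided t-test needs 27. Only the Laplace case comes near 21, and the article names no such distribution.

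**Step 4. If 0.5 is in VAS points.** The SDs are assumptions, because the article gives none.

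| SD of paired difference (points) | n for 80% power | Power with 21 |
|---|---|---|
| 0.5 | 10 | 99% |
| 0.775 | 21 | 80% |
| 1 | 34 | 59% |
| 2 | 128 | 19% |
| 3 | 285 | 11% |

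**Step 5. The 50% expectation in points.** For a placebo mean of m points, a 50% drop is 0.5 × m. Its ratio to 0.5 points is (0.5 × m)/0.5 = m, so the ratio equals the placebo mean, which the article does not state.

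| Assumed placebo mean | 50% drop (points) | Ratio to 0.5 | Power with 21, assumed SD 2 |
|---|---|---|---|
| 1 | 0.5 | 1 | 19% |
| 2 | 1.0 | 2 | 59% |
| 3 | 1.5 | 3 | about 90% |
| 5 | 2.5 | 5 | over 99% |

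At a placebo mean of 5, power for the 2.5-point drop is 95% with SD 3 and 78% with SD 4.

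**The case against.** The strongest reply is that the clause is loose wording. The opening of the same paragraph, the Outcomes section and the abstract all name antioxidant against placebo, so the 0.5 may have been meant as the treatment difference in pre-to-post change. That is possible, but the article does not say so. Even on that reading the unit and SD are missing, and 21 still depends on an SD near 0.78.

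Several stronger readings are tempting, and the article does not support them:

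- **A five-fold gap between the two targets.** This needs 0.5 to be in VAS points and a placebo mean of 5 on study nights. The 5 is an eligibility floor for past tinnitus, not an expected score 1 hour after exposure. The 0.5 might also be a standardised effect, or the 50% written as a proportion.
- **Two targets that cannot both stand because of their size.** A minimal clinically relevant difference may properly be smaller than the effect hoped for, and sizing on the smaller is conservative. What is wrong is the contrast and the missing link, not a gap in size.
- **No coherent primary contrast, and an uninterpretable result.** The treatment contrast is named in several places. The mixed-model estimate and its confidence interval can be read whatever the power statement says.
- **An analysis of raw change scores.** None is specified. The outcome is the VAS score, a mixed model is named, and full specification is promised before unmasking.
- **A true power of 19%.** That figure rests on one assumed SD. Each participant has two exposures per treatment, and averaging them lowers the SD. If nights vary independently and the treatment effect is the same in everyone, an SD of 0.78 for the difference of two-night means corresponds to 0.78 × √2 = 1.10 for a single pair of nights.

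These points limit the claim. They do not remove the mismatch between the stated purpose of the calculation and the effect entered in it.

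**Conclusion.** The concern holds in a limited form. The sample size section contradicts itself on the contrast: its purpose is treatment against control, but its effect is worded as before against after noise. The 50% hypothesis in *Outcomes* is not connected to it. The stated 80% power therefore has no demonstrated link to the primary hypothesis. This is a contradiction in a figure that the trial relies on, not a detail left to a fuller document.

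Its size cannot be fixed from the article. Under the named t-test, 80% power with 21 participants requires 0.5 to be in points with an SD of about 0.78. A standardised 0.5 gives about 59%. A 0.5-point target gives 59%, 19% or 11% for assumed SDs of 1, 2 or 3. If the 50% drop is the target and the placebo mean is well above 1, power could be ample. The article does not show which case applies.

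**What to change.** Restate the power calculation for one primary contrast: the antioxidant-minus-placebo difference in VAS 1 hour after noise, from the mixed model with the same night's pre-noise VAS as a covariate. Then:

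1. Give the target difference in VAS points and the SD that it is judged against. Say whether that SD refers to one night per treatment or to the mean of two.
2. Remove the pre/post wording from the power statement, and name one test in place of both a paired t-test and a non-parametric calculation.
3. Report the power that 21 participants deliver for that target, without enrolling more.
4. Say in *Outcomes* how the 50% expectation relates to the target, with the placebo mean that it assumes.

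The cost is rewording and one recalculation. The pre-noise VAS is already collected each night, so the covariate needs no new data, although its gain will be small if pre-noise scores vary little. The downside is that the stated power may become less favourable than 80%.

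### The 21 participants at 80% power cannot be reproduced from the stated inputs, and the calculation conflicts with itself and with the trial's comparison and expected effect

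*Protocol article*

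**What the plan says.** All references are to the protocol article.

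- **Sample size calculation and statistical analyses, test and error rates.** The aim is to detect a VAS difference between the experimental and control conditions, using G-Power. "A two-sided paired *t*-test for mean differences was performed", and "an α-level of 0.05 and a nominal power of 80% were used".
- **Same section, effect and result.** The effect is introduced as "Assuming a minimal difference of clinical effect of 0.5 between the pre- and post-noise measurements on the VAS". The sentence ends: "a non-parametric calculation showed a requirement of 21 participants". The non-parametric test is not named, and no SD, correlation or standardised effect is printed.
- **Same section, analysis.** Because measurements within a participant are correlated, "a mixed effects model will be applied".
- **Design.** There are four exposure nights, and "each participant will receive twice the antioxidants as well as the placebo".
- **Outcomes.** The expected effect is tinnitus loudness 50% lower on antioxidant than on placebo.
- **Visual analogue scale.** Loudness is scored from 0 to 10, once before and once after exposure.

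**The concern.** This paragraph is the only support for the 80% power claim on the primary outcome, and a reader cannot get from its inputs to its result. There are four problems:

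1. A paired t-test is named as the calculation, but the number is credited to an unnamed non-parametric one.
2. The 0.5 has no SD, and it is unclear whether it is in VAS points or standardised.
3. The 0.5 is a change from before to after noise within a night. The comparison to be powered is antioxidant against placebo.
4. The effect expected under Outcomes is of a different kind and probably of a different size.

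At stake is how a null result is read. With 80% power on record, a non-significant difference in 21 people may be taken as good evidence against a worthwhile effect. Whether that is fair depends on inputs that the article does not give.

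**Working it through.** **Inputs from the article:** two-sided alpha 0.05, power 80%, paired comparison, effect 0.5, n = 21, two nights per treatment.

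**Inputs not in the article (assumptions, shown as ranges):** the SD of the paired difference, the shape of its distribution, and the participant-by-treatment variation.

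**Method.** With d = difference / SD of the paired difference, paired t-test power comes from the noncentral t distribution with n − 1 degrees of freedom and noncentrality d√n. For the Wilcoxon signed-rank test, n is replaced by n × ARE, where ARE is the asymptotic relative efficiency: 3/π = 0.955 for normal data, 1.097 logistic, 1.5 Laplace, and 0.864 as the minimum.

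**Step 1. Try to reproduce 21 with 0.5 as a standardised effect, one pair per person.** For n = 21 the noncentrality is 0.5 × √21 = 2.29, against a critical value of 2.09 on 20 degrees of freedom.

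| Test (two-sided) | n for 80% power | Power at n = 21 |
|---|---|---|
| Paired t | 34 | 58.7% |
| Wilcoxon, normal | 35 | 56.6% |
| Wilcoxon, logistic | 31 | 63.1% |
| Wilcoxon, Laplace | 23 | 77.5% |
| Wilcoxon, minimum ARE | 39 | 52.0% |

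One-sided versions give 27 (t), 28 (normal), 24 (logistic), 18 (Laplace) and 31 (minimum ARE). No single-pair version gives 21.

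**Step 2. Read 0.5 as VAS points.** No n can be computed without an SD, so solve for the SD that makes 21 correct. Power of 80% at n = 21 needs d = 0.643 (t) or 0.659 (Wilcoxon, normal). The implied SD of the paired difference is 0.5 / 0.643 = 0.78 or 0.5 / 0.659 = 0.76.

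**Step 3. Power at n = 21 for 0.5 VAS points over a range of assumed SDs (t-test).** With two independent pairs per person and no participant-by-treatment variation, averaging multiplies d by √2.

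| Assumed SD of one paired difference | One pair per person | Two independent pairs |
|---|---|---|
| 0.75 | 83% | 98% |
| 1.0 | 59% | 87% |
| 1.5 | 31% | 54% |
| 2.0 | 19% | 34% |

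The columns are different designs and should not be merged into one range. Participant-by-treatment variation would put the two-night power below the right-hand column.

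**Step 4. Other routes to 21.** At d = 0.5 per pair with two independent pairs (d = 0.5 × √2 = 0.707), the required n is 18 (t), 19 (Wilcoxon, normal) or 21 (Wilcoxon, minimum ARE; 81% power). An SD of 1 per measurement with a correlation of 0.7 also gives 21 for a single pair: the SD of the difference is √(2 × 0.3) = 0.77. None of these assumptions is printed.

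**Step 5. The effect in Outcomes.** Eligibility requires past temporary tinnitus of at least 5 on the VAS. If placebo nights averaged about 5 (an assumption), a 50% drop is 2.5 points, five times 0.5. Single-pair power at n = 21 is then above 99% at SD 2, 95% at SD 3 and 88% at SD 3.5.

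**The case against.** The strongest defence is that nothing here proves an arithmetic error. The text puts 0.5 on the VAS, so the literal reading is VAS points. The answer then turns on an SD that a journal article may leave to the full protocol, and an SD near 0.76 to 0.78 gives 21. Two pairs per person under the minimum-ARE option also give exactly 21, so the number is reachable by a non-parametric route. Naming a t-test and a non-parametric method together need not conflict, since a signed-rank sample size can be obtained from the t-test one by an ARE adjustment. Sizing on a paired test and analysing with a mixed model is common practice.

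Most of this stands. A reader might infer that 21 is simply the wrong answer and that 34 or 35 is the right one. The article does not support that: those figures hold only for a standardised effect and one pair per person, and neither is stated. A reader might also infer that the trial is underpowered. That is not shown either, given Steps 3 to 5.

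What the defence does not reach is the printed text itself. The 0.5 is attached to the pre- versus post-noise change rather than to the treatment contrast, and a different expected effect appears under Outcomes. Leaving detail to a fuller document does not explain either. Nor can a reader tell which of several incompatible routes produced 21.

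**Conclusion.** The point holds as one of reproducibility and internal consistency. The 21 participants at 80% power cannot be reproduced from the paragraph. Its effect is not defined on the comparison it sets out to power, and it is not reconciled with the halving expected under Outcomes.

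The size of the problem depends on the reading. A standardised single-pair effect leaves power at 59% (t) or 57% (Wilcoxon, normal) instead of 80%. A raw 0.5 points makes the 80% claim depend on an unstated SD: single-pair power falls from 83% at SD 0.75 to 19% at SD 2.0, and the two-pair figures from 98% to 34%. The SDs are assumptions, and the article favours none of them. The result does not establish that 21 is inadequate, only that the stated power has no checkable basis.

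**What to change.** Keep n = 21 and replace the paragraph with one calculation for the antioxidant-minus-placebo contrast, with two nights per treatment, under the planned mixed model. It should:

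- name one test, or the model contrast itself;
- give the difference in VAS points between treatments and reconcile it with the 50% drop;
- state the within-participant SD and the participant-by-treatment variance assumed;
- restate the power that 21 participants deliver over a range of SDs.

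Half of the needed participants were already included when the article was written, so a pooled SD computed without treatment labels can inform the SD and leave the blind intact. The article says that the main analysis will be fully specified before unmasking, and this revision fits there.

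The cost is rewording and about an hour of computation, with no extra participants and no change to the design. The drawback is that the restated power may be less favourable than 80%.
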